# Efficacy of manual acupuncture versus placebo acupuncture for generalized anxiety disorder (GAD) in perimenopause women: study protocol for a randomized controlled trial

**DOI:** 10.1186/s13063-021-05756-x

**Published:** 2021-11-24

**Keywords:** Generalized anxiety disorder, Acupuncture, Protocol

## Abstract

**Background:**

Generalized anxiety disorder (GAD) is common among perimenopausal women. Acupuncture may be an effective treatment for GAD, but evidence is limited. The pathogenesis of GAD is not yet clear, but it is related to the hypothalamic-pituitary-adrenal axis and its excretion, cortisol (CORT), and adrenocorticotropic hormone (ACTH). The object of this study is to evaluate the efficacy of manual acupuncture (MA) versus placebo acupuncture (PA) for perimenopausal women with GAD.

**Methods:**

This study is a single-center, randomized, single-blind clinical trial that will be conducted in the First Affiliated Hospital of Guangzhou University of Chinese Medicine. A total of 112 eligible GAD patients will be randomly assigned (1:1) to receive MA (*n*=56) or PA (*n*=56) three times per week for 4 weeks. The primary outcome measure will be the HAMA score. The secondary outcome measures will be the GAD-7 and PSQI scores and the levels of CORT and ACTH. The evaluation will be executed at baseline, 2 weeks, the end of the treatment, and a follow-up 3-month period. All main analyses will be carried out based on the intention-to-treat (ITT) principle.

**Discussion:**

This study intends to compare the efficacy between MA and PA in the treatment of perimenopausal women with GAD and to further study the mechanisms underlying the effect.

**Trial registration:**

Chinese Clinical Trial Registry ChiCTR2100046604. Registered on 22 May 2021.

## Background

Generalized anxiety disorder (GAD) is a kind of chronic mental disorder that includes both mental and physical symptoms [1]. GAD patients have general apprehensiveness or worry that is not restricted to any particular stimulus as the primary clinical feature [2]. According to epidemic research in Europe, the incidence rate of GAD is 6.2% throughout the lifetime [3]. Moreover, females have 1.5 to 2 times more exposure to GAD than males [4]. To our knowledge, the prevalence of females aged between 45 years old and 54 years old is the highest [5]. This phenomenon indicates that perimenopausal women are more likely to suffer from GAD. As one of the first-line pharmacotherapies for GAD [6], serotonin reuptake inhibitors (SSRIs) inhibit the reuptake of serotonin to increase the concentration of serotonin in the synaptic cleft to improve the level of serotonin in the brain which is believed to attenuate anxious symptoms [7]. However, patients’ conditions might be aggravated in the first week when first taking SSRIs [8]. Therefore, some patients refuse to take drugs because of adverse events. They seek for the help of psychiatrists and some of them probably receive cognitive behavioral therapy (CBT). Studies [9, 10] have shown that CBT is an effective treatment for GAD. However, due to the shortage of professionals and high cost, CBT is not beneficial for most patients in China [11]. Therefore, patients turn to find help from alternative therapies such as acupuncture.

Although the pathogenesis of GAD is not yet clear, current studies believe that it is related to abnormal secretory function of the hypothalamic-pituitary-adrenal axis (HPA axis) [12]. Cortisol (CORT) synthesized by the adrenal cortex is one of the final products of the HPA axis. CORT and adrenocorticotropic hormone (ACTH) levels in GAD patients are higher than those in normal people [13, 14]. The elevation of CORT and ACTH is detected as negative feedback by the hypothalamus which downregulates the stress response [15, 16]. Therefore, the decline in CORT and ACTH levels could predict the degree of improvement that a treatment produces [17].

Therefore, we designed a randomized controlled trial that focus on the efficacy of manual acupuncture (MA) versus placebo acupuncture (PA) on GAD in perimenopausal women. To evaluate the therapeutic efficacy of GAD, the primary outcome measure used in our protocol is the change in scores on the Hamilton Anxiety Scale (HAMA). The secondary outcome measures are the changes in scores on the Generalized Anxiety Disorder Scale (GAD-7) and Pittsburgh Sleep Quality Index (PQSI), and laboratory indicators related to the current possible pathogenesis of GAD, mainly including CORT and ACTH. This protocol aims to explore the efficacy of MA in GAD patients who would not prefer drug or CBT therapies. Meanwhile, we hope to explore the possible mechanism of acupuncture on GAD by measuring the levels of CORT and ACTH in serum.

## Methods

### Study design

This is a randomized controlled and patient-and-assessor-blind trial. A total of 112 participants will be enrolled from the outpatient Acupuncture and Moxibustion Department of the First Affiliated Hospital of Guangzhou University of Chinese Medicine. The flow chart is shown in Fig. 1. The protocol is composed based on the SPIRIT checklist [18] and the Declaration of Helsinki [19]. The trial was approved by the Ethics Committee of the First Affiliated Hospital of Guangzhou University of Chinese Medicine (K[2021]014) and has been registered at the Chinese Clinical Registry (ChiCTR2100046604).

**Fig. 1 Fig1:**
[figure not shown]
Flow chart

### Sample size

According to preliminary trials [20, 21], we chose the HAMA score as the outcome to calculate the sample size. After treatment, the HAMA score of MA was 14.0±3.2, and the HAMA score of PA was 19.4±5.3. PASS version 15.0 (NCSS, LLC. Kaysville, UT, USA) was used to estimate the sample size with a power level of 90% and a two-sided significance level of 5%. After calculation, we set the sample size of 44 patients in each group to observe the significant difference between the two groups. With a 20% withdrawal rate, we plan to enroll a total of 112 patients with 56 patients in each group.

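### The stated 44 patients per group does not follow from the stated inputs, which need 15 or 16 per group for 90% power (22 with the larger SD in both arms)

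*Protocol article*

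**What the plan says.** The Sample size section of the protocol article rests the calculation on HAMA ("we chose the HAMA score as the outcome to calculate the sample size") and takes the post-treatment values from preliminary trials: "the HAMA score of MA was 14.0±3.2, and the HAMA score of PA was 19.4±5.3". PASS 15.0 was run "with a power level of 90% and a two-sided significance level of 5" per cent. The result is given as follows: "After calculation, we set the sample size of 44 patients in each group to observe the significant difference between the two groups". The only later adjustment is for attrition ("With a 20% withdrawal rate"), which brings the target to 56 per group and 112 in total. The Randomization and allocation concealment section confirms 1:1 allocation. The total of 112 also appears in the Abstract and under Study design and Patient recruitment. No section gives another effect size, SD, margin or reason that would lead to 44, and the PASS procedure and the test are not named.

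**The concern.** The paragraph supplies everything a two-mean calculation needs, so its result can be checked. A difference of 5.4 points against SDs of 3.2 and 5.3 is a standardised effect above 1.2, which 90% power detects with a small trial. The stated 44 is about 2.8 to 2.9 times what the inputs require (44/16 = 2.75; 44/15 = 2.93).

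This paragraph is the only quantitative basis for the size of the trial. If the stated inputs are the ones used, about 38 to 40 patients would have been enough after the 20% withdrawal allowance, and the case for enrolling 112 is not made. If other inputs were used, the paragraph does not describe the trial that was planned. In either case the quoted 90% is not the power of this design for the quoted difference.

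**Working it through.** **Inputs** (Sample size section unless noted): means 14.0 and 19.4; SDs 3.2 and 5.3; power 90%; two-sided 5%; 44 per group before withdrawal; 20% withdrawal; 56 per group enrolled; 1:1 allocation (Randomization and allocation concealment).

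**1. Effect size.** Difference = 19.4 − 14.0 = 5.4. Pooled SD = √[(3.2² + 5.3²)/2] = √[(10.24 + 28.09)/2] = 4.38. Standardised effect = 5.4/4.38 = 1.23.

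**2. Attempt to reproduce 44, normal approximation.** n per group = (1.960 + 1.2816)² × (3.2² + 5.3²)/5.4² = 10.51 × 38.33/29.16 = 13.8, so 14.

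**3. Noncentral-t power for the stated inputs.**

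| Calculation | n per group | Power |
|---|---|---|
| Pooled t | 15 | 90.3% |
| Welch t | 15 | 89.9% |
| Welch t | 16 | 91.8% |
| SD 5.3 in both arms | 21 | 89.6% |
| SD 5.3 in both arms | 22 | 91.0% |

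The requirement is therefore 15 (pooled) or 16 (Welch), and 22 on the most conservative reading of the stated SDs.

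**4. Other routes to 44 at two-sided 5% and 90% power.** Inflating for a rank test (relative efficiency 0.955 or 0.864) gives 16 to 19 from the stated SDs, and 24 to 26 with SD 5.3 in both arms. Combining the SDs wrongly as √(3.2² + 5.3²) gives 29; adding them (8.5) gives 54. None gives 44.

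**5. Power at 44 per group for 5.4 points.** Pooled or Welch t: 99.99%. SD 5.3 in both arms: 99.7%.

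**6. What 44 per group detects at 90% power.** Solving the t-test for the effect gives a standardised effect of about 0.70. That is 0.699 × 4.38 = 3.1 points at SD 4.38, or 0.699 × 5.3 = 3.7 points at SD 5.3. For 5.4 points to need 44 per group, the SD would have to be about 5.4/0.699 = 7.7.

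**7. Withdrawal step.** 44/0.8 = 55, against 56 stated. This step is sound to within one patient per group, so attrition does not explain the gap. Applied to the recomputed numbers: 15/0.8 = 18.75, so 19; 16/0.8 = 20; 22/0.8 = 27.5, so 28 per group. The totals are 38, 40 and 56.

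**8. A coincidence worth checking.** With SD 5.3 in both arms, 22 per group is 44 in total, and 28 per group after withdrawal is 56 in total. Both match the article's per-group figures. This would fit totals having been read as per-group numbers, but the document cannot show that it happened.

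**The case against.** The strongest reply is that the discrepancy is in the safe direction. Under the plan's own assumptions the trial has well over 90% power, and the type I error, allocation and analysis are unaffected. A null or smaller result will be read mainly from its estimate and confidence interval, which do not depend on this paragraph. All of that stands. It limits the consequence, but does not make the paragraph correct.

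A second reply is that the article names neither the PASS procedure nor the test, so 44 may include a deliberate increase or an unreported input. For example, a superiority margin of about 2.3 points (5.4 − 3.06 = 2.34) would give about 90% power at 44 with these SDs. This cannot be excluded, so one cannot say which element is wrong. But the text presents 44 as the outcome of the calculation, mentions no margin or increase, and describes only the withdrawal allowance, which is applied afterwards.

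The brevity of a journal article is no answer either: nothing is being called missing. Figures printed in one paragraph disagree.

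A reader might go further and infer that the target effect is unknown, or that the trial is really sized for about 3.1 points. The document supports neither. It states an effect, 5.4 points; what is unknown is the input that produced 44. The 3.1 is back-solved from n = 44 and appears nowhere in the article. It also depends on the SD: at SD 5.3, 44 per group has only about 77% power for 3.1 points.

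**Conclusion.** The point holds: 44 per group at 90% power cannot be reproduced from the stated means, SDs and significance level. Those need 15 or 16 per group, or 22 with SD 5.3 in both arms. The power at 44 per group for the stated difference is about 99.99% (99.7% with SD 5.3 in both arms). Either the stated 90% is wrong for this n, or the calculation used something the paragraph does not report.

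This assumes a two-sample comparison of post-treatment means with 1:1 allocation, which is what the stated inputs describe. It is not a finding of low power, and the document does not establish that 112 was a mistake. The possibility that totals were taken for per-group numbers is a reason to look at the PASS output, not a conclusion.

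**What to change.** Keep 112 patients. Retrieve the PASS output and check it, including whether 44 and 56 were totals. Then correct the Sample size section by naming the PASS procedure and the effect, SD or margin actually entered.

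- If the inputs differ from those printed, print the ones used and give their source.
- If the printed inputs are the ones used, say that they require 15 to 16 per group for 90% power, and that 44 evaluable patients per group give over 99% power for a 5.4-point difference.
- If the sponsor wishes to say what 44 per group detects at 90% power (standardised effect about 0.70: 3.1 points at SD 4.4, 3.7 points at SD 5.3), label it as the detectable difference at the chosen n. Enrolment is already under way according to the Trial status section, so presenting such a figure as the planned effect would be fitting a target to a fixed n.

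The cost is one look at the software output and one reworded paragraph, with no change to patients or procedures.

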### Randomization and allocation concealment

An independent researcher sets a random number as a seed and used IBM SPSS Statistics version 26 (IBM SPSS Inc., Chicago, USA) to generate a random allocation sequence. According to the size of the random number sequence, patients who received the first 56 random numbers will be allocated into the MA group, and patients who received the last 56 random numbers will be allocated into the PA group in a 1:1 ratio. The researcher will put the cards with written random numbers and group assignments into sealed envelopes. The intervenors will allocate enrolled patients into the MA group or PA group on the basis of the card in the envelope.

### Blinding

Due to the nature of acupuncture, it is difficult to blind patients and intervenors at the same time. We designed a new placebo acupuncture needle pedestal to blind patients, and the pedestal was applied for a patent in China (202121352221.7). The new placebo needle can be used at different positions with the acupoints and at different needling angles (Fig. 2). The PA group used a special needle (φ0.30 × 40 mm, produced by Huanqiu Co. Ltd., China) in which the tip is blunt so that the needle could not be pricked into the skin. In addition, the diameter of the blunt needle is 0.3 mm. It is thin enough to make patients feel like they are pricked. The pedestal is opaque so patients would not know whether the needle is pricked. Therefore, patients are unaware of whether they receive MA or PA. In addition, there is adhesive tape below the base to ensure that the whole pedestal can adhere to the head and body (Fig. 3). To test the participant-blinding effects, the first two patients will be randomly selected from the study to guess whether they have received MA or PA within 5 minutes after one of the treatment sessions in weeks 2 and 4. In addition, researchers who analyze the data are unaware of group assignments either to minimize the potential source of bias.

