### Placebo acupuncture (PA) group

Patients in the PA group will receive placebo acupuncture in which the needles will not be inserted into the skin and will not induce the Deqi sensation. The blunt-tipped placebo needle (φ0.30 × 40 mm, produced by Huanqiu Co. Ltd., China) can provide participant-blinding effects with a similar appearance to conventional needles but no skin penetration.

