This study has room for improvement. First, due to the nature of acupuncture, we spare no effort to maintain blinding, but we still cannot find a perfect way to achieve double blinding. We can make the pedestal of acupuncture needles that look the same and simulate the feeling of being needled by touching with semi blunt needles. Therefore, patients are unaware of whether they receive MA or PA. However, experienced acupuncturists can feel the difference in whether needles prick the skin and achieve Deqi or not. Second, this study is a single-center trial, and we hope that this study will provide more clinical evidence and design a multi-center trial to confirm the efficacy of acupuncture in treating GAD.

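### The check on participant blinding uses two of 112 patients, chosen by a rule that contradicts itself, so it cannot show whether blinding worked

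*Protocol article*

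**What the plan says.** The Blinding section of the protocol article introduces a new control device ("We designed a new placebo acupuncture needle pedestal to blind patients") and then a check on it. The purpose is explicit: "To test the participant-blinding effects". The timing is explicit too, with guesses taken following a session in week 2 and another in week 4. So is the sample: "the first two patients will be randomly selected from the study to guess whether they have received MA or PA within 5 minutes". No other section describes a wider check, a number per arm or a criterion for success.

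Both the Blinding section and the Discussion treat the result as settled; in the words of the latter, "Therefore, patients are unaware of whether they receive MA or PA".

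The two arms are meant to feel different. Under MA group, needles go in about 25–30 mm and are manipulated at three points in each session until Deqi is felt. Under Placebo acupuncture (PA) group, treatment is one "in which the needles will not be inserted into the skin and will not induce the Deqi sensation".

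On size, the Sample size section says: "we plan to enroll a total of 112 patients with 56 patients in each group".

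**The concern.** There are two defects in one sentence.

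1. **The selection rule contradicts itself.** Order of entry fixes who the first two patients are, which leaves nothing to draw at random. Staff cannot carry out both instructions.
2. **Two patients cannot serve the stated purpose.** Whatever they answer, the result fits both perfect blinding and severe unblinding.

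What is at stake is the reading of the placebo comparison. The opaque base hides the needle from view but not a difference in sensation that the protocol builds in. The therapists know the allocation, so protection against expectation effects rests on the patient and the assessor. GAD-7 and PSQI are questionnaires, and HAMA depends in part on what the patient reports. The Discussion also gives as an aim to find out whether acupuncture has a placebo effect, which is hard to interpret if nobody can say how many patients knew their arm.

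The guesses have to be collected during treatment. Under Ancillary and post-trial care, PA patients are later given 12 MA sessions as compensation, which reveals their allocation.

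**Working it through.** **Inputs**
- Patients asked: 2 (Blinding).
- Occasions: weeks 2 and 4, so at most 2 guesses per patient and 4 in all (Blinding).
- Randomised: 112, 56 per arm (Sample size). Planned after withdrawal: "we set the sample size of 44 patients in each group to observe the significant difference between the two groups", so 88 in total.
- Two-sided significance level 0.05 (Data monitoring and analysis).
- Assumption: with two options and 1:1 allocation, a fully blinded patient is right with probability 0.5. The article gives no benchmark.

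The article derives the number two from no calculation, so there is no figure to reproduce. What can be checked is how much information two guesses carry.

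**Step 1. Exact (Clopper–Pearson) 95% CI and exact p against 0.5**

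| Correct of 2 | Formula for the limits | 95% CI | Two-sided p |
|---|---|---|---|
| 0 | upper = 1 − √0.025 | 0–84.2% | 2 × 0.5² = 0.50 |
| 1 | lower = 1 − √0.975; upper = √0.975 | 1.3–98.7% | 1.00 |
| 2 | lower = √0.025 | 15.8–100% | 2 × 0.5² = 0.50 |

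Every interval contains 50%. The smallest possible p-value is 0.50, so power at the 5% level is zero against any degree of unblinding. Two blinded patients are both right by luck with probability 0.5² = 0.25.

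**Step 2. Counting both occasions.** Treating weeks 2 and 4 as four independent guesses is generous, because each patient answers twice. Even so, 4 of 4 correct gives 2 × 0.5⁴ = 0.125. Six independent guesses are the fewest that can reach significance: 2 × 0.5⁶ = 0.031.

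**Step 3. Coverage of the arms.** P(both in the same arm) = 2 × C(56,2) / C(112,2) = 2 × 1540 / 6216 = 55/111 = 49.5%. This holds for the first two patients or for a random pair under the 56:56 allocation. If the two do fall in different arms, each arm has one guess and a 95% CI of 0–97.5% or 2.5–100%.

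**Step 4. What asking everyone would give.** Exact 95% CI for forced two-way guesses with 50% correct:

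| Guesses | 95% CI | Power at a true 65% / 70% correct |
|---|---|---|
| 112 (all randomised) | 40.4–59.6% | 0.89 / 0.99 |
| 88 (planned completers) | 39.1–60.9% | 0.80 / 0.97 |
| 56 (one arm) | 36.3–63.7% | – |
| 44 (one arm, completers) | 34.6–65.4% | – |

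These figures do not carry over directly once a don't-know answer is allowed, since 50% correct is then no longer the natural benchmark. The arm-wise Bang index (share guessing right minus share guessing wrong) keeps zero as its reference. Near zero, and with no don't-know answers, its half-width is 1.96 × 2 × √(0.25/n): 0.26 for n = 56 and 0.30 for n = 44.

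**The case against.** **The number may be a slip of language.** The sentence is garbled, the full protocol is not shown, and the authors may have meant two patients per week, session or therapist. That is possible and lowers certainty about the intended number. But nothing in the article supports a larger scheme, and the sentence would need correcting on that reading as well. This is a stated rule, not a detail left to another document.

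**The check changes nothing else.** This stands. The statistical section shown does not use the guesses, and they affect no allocation, outcome or test. Asking all patients would measure unblinding, not prevent it; the difference in sensation would remain.

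**Guesses at weeks 2 and 4 are mixed with benefit.** This also stands. A patient may guess MA because she feels better, so even a full survey cannot cleanly separate unblinding from efficacy.

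**Other safeguards exist.** An assessor unaware of assignment collects the outcomes (Outcome measure), and the Discussion says the device is meant to imitate the feel of needling. Both help, but assessor blinding does not remove a patient's own expectation from what she reports, and the imitation is an intention for which no data are given.

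A reader might infer three stronger things that the article does not support:
- *The pedestal was never tested.* The article calls it new and mentions a patent application. It gives no blinding data, but does not say that none exist.
- *The patients know acupuncture and will recognise Deqi.* Enrolment is in an acupuncture outpatient department and previous acupuncture is not an exclusion, but Patient recruitment also lists posters, WeChat, gynecology and psychology. Prior experience is unknown.
- *Any MA–PA difference would be mere expectation.* Nothing in the article shows that blinding fails.

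**Conclusion.** The point holds on the text as written: the selection rule contradicts itself, and two of 112 patients (1.8%) cannot test blinding. No possible result excludes 50% correct or reaches p<0.05, and in almost half of all possible pairs one arm is not assessed at all. The statement that patients are unaware of their allocation would therefore remain unsupported by the trial's own check.

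The conclusion takes the literal number two and a chance rate of 0.5. Counting the two occasions as independent does not change it.

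This should be fixed and is cheap to fix, but it is not an error that invalidates the primary comparison. The defect is in a diagnostic; it is not evidence that blinding fails.

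**What to change.** Replace the sentence on the first two patients with the following:
- Every participant still to be treated is asked, within 5 minutes after one session in week 2 and one in week 4, to guess MA, PA or don't know, and to give the reason.
- A blinding index is reported by arm with its 95% CI at each time point, not a pooled percentage correct.
- The week 2 results and the stated reasons are shown separately, and the report says that guesses made after treatment has begun partly reflect perceived benefit.

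Until such results exist, the Blinding and Discussion sections should describe patient blinding as intended, not as achieved.

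The cost is one short question at two sessions that already take place, with no change to treatment, staff or sample size. Trial status reports the trial as already running, so patients already treated cannot be recovered and precision will fall short of the figures for 56 or 44 per arm by an amount that the article does not allow one to state. As an illustration only, if half remained (28 per arm), the approximate half-width at 50% correct would be 1.96 × √(0.25/28) = 0.185, about ±19 points per arm. That is still far more than two guesses can give.

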### Inventions

All eligible patients will receive 12 sessions of MA or PA (4 weeks, three times a week). Each session will take 30 min. The acupuncture therapists have acupuncture education from Guangzhou University of Chinese Medicine (range 1–3 years of full-time academic studies) or have clinical experience in the First Affiliated Hospital of Guangzhou University of Chinese Medicine (range 2–5 years). In addition, all intervenors are trained to completely understand the standard of operation. The acupoints of the MA and PA groups are the same, including Sishenzhen (one of the main acupoints in Jin’s 3 Needle [22]), Shenting (DU24), Yintang (DU29), Shenmen (HT7), and Sanyinjiao (SP6). The acupoint locations are according to the “2006 People’s Republic of China National Standard” (GB/T1234-2006) with the exhibition in Fig. 4. The acupuncture operation will be performed according to the textbook of the 10th Five-Year Plan of the Ministry of Health. Enrolled patients will be treated one-on-one by a trained acupuncturist from beginning to the end. In addition, an independent assistant will follow the intervention procedures to ensure the consistency of treatment.

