### Primary outcome

#### HAMA score

The primary outcome of this study is the HAMA [25] score, which measures the severity of anxiety. The HAMA is a 14-item scale rated on a 4-point scale with a total score ranging from 0 to 56. A higher score means a higher range of anxiety. According to studies, a score higher than 28 indicates severe anxiety, a score between 28 and 21 indicates moderate anxiety, a score between 20 and 14 indicates mild anxiety, and a score lower than 14 indicates no anxiety. HAMA will be assessed on the first day, the 14th day, and the 28th day of the trial.

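### Patients guess their arm only in weeks 2 and 4, so above-chance guessing in a trial where acupuncture works could mean a failed blind or felt benefit

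*Protocol article*

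**What the plan says.** The Blinding section of the protocol article describes a new opaque pedestal and a blunt needle, meant to make placebo acupuncture (PA) look and feel like manual acupuncture (MA). To check that this works, patients are to "guess whether they have received MA or PA within 5 minutes after one of the treatment sessions in weeks 2 and 4". On who is asked, it says "the first two patients will be randomly selected from the study". No guess after the first session is stated, and no question on the reason for the guess.

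Three other places bear on this:

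- **Treatment schedule (section headed Inventions):** 12 sessions over 4 weeks, three a week.
- **Primary outcome (HAMA score):** "HAMA will be assessed on the first day, the 14th day, and the 28th day of the trial".
- **Expected effect (Sample size):** after treatment, "the HAMA score of MA was 14.0±3.2, and the HAMA score of PA was 19.4±5.3".

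The MA and PA group sections add that the arms differ in sensation: MA needles are manipulated until Deqi occurs, and PA does not induce it.

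**The concern.** The properties that are supposed to blind the patient are appearance and sensation. Both are present at session 1. The check instead falls in the weeks of the two post-baseline HAMA ratings under treatment, when a patient may have noticed whether her anxiety has eased. A patient who feels better has a reason to guess MA even if the device conceals the allocation perfectly.

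Felt benefit and a failed device can therefore leave the same trace, namely more correct guesses than chance. This matters because the device is new and because the Discussion presents the trial as evidence on the placebo effect of acupuncture. A positive trial with above-chance guesses would face the criticism that patients knew their arm. Late guesses alone could neither confirm nor rebut it.

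**Working it through.** The plan gives no figure for the blinding check, so there is none to reproduce. The planned sample size is not an input.

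**1. Timing.** At three sessions a week, week 2 contains sessions 4 to 6 and week 4 contains sessions 10 to 12. A patient has completed at least four sessions before she is first asked. Day 14 and day 28 fall in the same two weeks.

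**2. How far benefit alone could move the guesses.** Inputs from Sample size: MA mean 14.0, SD 3.2; PA mean 19.4, SD 5.3; difference 19.4 − 14.0 = 5.4. Assumptions (not in the documents): scores are normal, the device blinds perfectly, and a patient who guesses from improvement says MA if her end-of-treatment HAMA is below a cut-off. The cut-off that gives the most correct guesses is 17.43.

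- MA correct: Φ((17.43 − 14.0)/3.2) = Φ(1.07) = 0.858
- PA correct: 1 − Φ((17.43 − 19.4)/5.3) = 1 − Φ(−0.37) = 0.645
- Average over equal arms: (0.858 + 0.645)/2 = 0.752

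The midpoint of the two means, 16.7, gives nearly the same average: Φ(0.84) = 0.801 in MA, 1 − 0.305 = 0.695 in PA, average 0.748.

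If only a share q guesses from improvement and the rest guess at random, the correct rate in an arm is 0.5 + q(p − 0.5), where p is that arm's rate at cut-off 17.43:

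| q | MA correct | PA correct | Overall |
|---|---|---|---|
| 0% | 50% | 50% | 50% |
| 25% | 59% | 54% | 56% |
| 50% | 68% | 57% | 63% |
| 75% | 77% | 61% | 69% |
| 100% | 86% | 65% | 75% |

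In the last row the by-arm blinding index (2 × correct − 1) is 0.72 in MA and 0.29 in PA, with the blind intact. The documents give no value for q.

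**3. Week 2.** The means above are post-treatment values. If half the difference were present in week 2 (assumption), the MA mean would be 19.4 − 2.7 = 16.7. The overall maximum would then be about 63% with the midpoint cut-off and 65% with the best one.

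**4. The number asked.** Taken as worded, two patients guess. Both correct has probability 0.5² = 25% by chance and 0.75² = 56% at the 75% rate. The exact 95% interval for 2 of 2 has lower limit √0.025 = 0.16 and upper limit 1. If the two were drawn at random from 112, they would come from the same arm with probability 2 × (56 × 55)/(112 × 111) = 0.50. With all 56 per arm, the 95% half-width around 50% is 1.96 × √(0.25/56) = 0.13.

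**The case against.** **The late timing has a purpose.** What threatens the primary outcome is what the patient believes when HAMA is rated, after repeated sessions. A guess after session 1 cannot detect unblinding that builds up over 12 sessions. This stands. It is a reason to keep the later guesses, and not a reason to omit an early one.

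**That improvement drives the guess is an inference.** Nothing in the article shows it. A guess within 5 minutes of a session may equally reflect needle sensation, since Deqi is sought in one arm only. The model above also uses the absolute final score, not change. Entry HAMA runs from 14 to 28, so a woman who falls from 28 to 18 is counted as guessing PA. This stands too: the percentages illustrate a possible range and are not predictions.

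**The number asked is the plainer fault.** Two guesses are uninformative at any time, and the wording is at odds with itself, because the first two patients are not a random selection. This stands, and moving the timing alone would not help. The converse also holds: asking everyone only in weeks 2 and 4 would leave the ambiguity.

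**The article is condensed.** A reason-for-guess item may exist in the full protocol or case report form. That is possible, but the timing is not left open here: the article fixes the weeks and even the minutes.

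**Conclusion.** The point holds in a limited form. If MA is effective and guesses in weeks 2 and 4 are above chance, the planned check cannot say whether the device failed or patients felt the benefit. Under the plan's own 5.4-point effect and a perfect blind, overall correct guesses could lie anywhere from 50% to about 75% at the end of treatment, and probably less far above chance in week 2. This rests on an assumed guessing rule and an unknown share of patients who use it.

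Three stronger readings are tempting but not supported:

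- **That the check can never separate the two explanations.** Near-chance guessing in an adequate sample, despite improvement, would support the blind.
- **That the check is uninformative if MA has no effect.** Improvement would then not differ between arms and could not produce a difference in guesses. Any excess of correct guesses would point to the needle or device, so the check is unconfounded in that case.
- **That the check will report unblinding and discredit a valid positive result.** With all 56 per arm asked and half guessing from improvement, a two-group test would be significant about 75% of the time (midpoint cut-off). No such test is in the plan, which asks two patients, and the article ties the guess to no analysis or decision rule.

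The matter is worth correcting because the remedy is cheap and makes the check interpretable. It does not affect the validity of the primary comparison itself.

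**What to change.** In the Blinding section:

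1. Add a guess (MA / PA / do not know) within 5 minutes after session 1.
2. Ask all patients in both arms at every time point, and remove the wording on the first two patients.
3. Keep the guesses in weeks 2 and 4.
4. Record the main reason for each guess: sensation or appearance, or improvement.
5. Report a blinding index by arm at each time. Use the session-1 result to judge the device and the later results to judge belief at the time of outcome rating.

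Do not adjust the later guesses for HAMA change. Change is measured after randomization and may itself be altered by unblinding, so the adjustment could hide the failure being looked for.

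The cost is two short case report form items at existing sessions, asked of all patients. A small downside is that asking early may make some patients think about their allocation. Trial status reports the trial as under way, with enrollment expected to end on May 1, 2022, so the session-1 guess could cover only patients not yet past that session when the change takes effect.
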